### Research design

2.1

This study is a cohort study with three measurement points conducted at 6- to 12-month intervals (*n* = 600). The impact of the health communication campaign will be evaluated by measuring indicators of knowledge, attitudes and practices related to burn first aid, as well as psychological variables and health information-seeking variables, among the following groups: the exposure group (i.e., burn survivors [*n* = 200] and caregivers [*n* = 100] exposed to campaign messages), the non-exposure group (i.e., burn survivors [*n* = 250] not exposed to campaign messages) and the Photovoice group (i.e., burn survivors [*n* = 50] who participate in Photovoice and are exposed to the campaign messages). Figure 1 presents the campaign process and the planned activities in different phases.

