##### Brief Resiliency Scale (BRS)

2.2.5.10

The BRS is a six-item self-report scale (47). Sample items include the following: ‘I tend to bounce back quickly after hard times’; ‘I have a hard time making it through stressful events’; ‘It does not take me long to recover from a stressful event’; and ‘It is hard for me to snap back when something bad happens’. The response options for all items are ordered on a five-point Likert-type scale. The scale demonstrated appropriate internal consistency, with Cronbach’s alphas ranging from 0.80–0.91 across four samples in the study (47).

The sample size calculation for the study is based on a comparison of the baseline and follow-up measures of the primary outcome, knowledge of burn-related prevention, in this cohort study. Using a previous study as a reference (22), we determined that a sample size of 478 is required to achieve a 70% improvement in knowledge of burn-related prevention, assuming a 63% rate of poor knowledge at baseline, a 5% significance level and 91.5% power at the 24-month follow-up (last follow-up). A total of 600 participants will be required, with a 20% dropout rate taken into account.

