## Data analysis plan

4

To compare changes in self-reported outcomes within groups across two time points (see Table 1) in the sample (*N* = 600), we will implement linear mixed-effects models implemented in R (R version 3.6.1) (51) using the lme4 package and in SAS 9.4. This method considers correlations within participants, allowing them to be modelled appropriately. It also estimates within-subject variability, in addition to estimating model parameters. The method can handle and model missing outcome data under the assumption that the data are missing at random. The mixed model uses a longitudinal data structure that includes both fixed and random effects, and baseline measurement is usually included as a covariate. Time will be included in the model as an interacting categorical variable to observe any time-varying trends. Cohen’s *d* for the effect of Photovoice will be calculated as the difference between baseline-corrected estimated means divided by the pooled standard deviation. A two-sided *p* < 0.05 indicates statistical significance. In addition, demographic variables, such as age, education, gender, marital status, geographic location (i.e., rural vs. urban residence) and household situation (i.e., living with a single and/or an extended family) will be included in the linear mixed models to test for potential moderating and mediating effects on behavioural intention related to burn prevention and first-aid practices. A stepwise selection of the variables will be conducted to determine which variables to keep in the model. As we add the variables, we will immediately eliminate those that do not reduce the Akaike information criterion (AIC) by using the *stepAIC* R function from the library *MASS*. If two or more independent variables in a model are found to be strongly correlated, a variance inflation estimate of less than 5 will be used to determine whether collinearity is present. If the relationship is found to be non-linear, attempts will be made to model the outcome data via the use of splines or polynomials in the *nlme* package in R. The normality of residuals will be assessed graphically using histograms and Q-Q plots. Detailed statistical analyses following Good Clinical Practice: Consolidated Guidelines ICH E9 (52) and Medical Research Council guidelines for developing complex interventions (53) will be described in the statistical analysis plan, which will be finalised before the data lock stage.

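### The 478 evaluable participants behind the stated 91.5% power include survivors defined as unexposed; if the planned improvement is the one in campaign recipients, about 280 are evaluable and power is about 72%

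*Protocol article*

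**What the plan says.** The sample-size paragraph (Protocol article, end of section 2.2.5.10, Brief Resiliency Scale) gives its basis as follows: "The sample size calculation for the study is based on a comparison of the baseline and follow-up measures of the primary outcome", that outcome being knowledge of burn-related prevention. It continues that "a sample size of 478 is required to achieve a 70% improvement in knowledge of burn-related prevention". The inputs listed for this number are poor knowledge in 63% of participants at the start, testing at the 5% level, and power of 91.5% for the final measurement at 24 months. The paragraph closes with "A total of 600 participants will be required, with a 20% dropout rate taken into account". No test is named, and neither a group nor a between-group contrast is mentioned.

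Section 2.1 (Research design) and the Abstract give the make-up of the 600:

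- exposure group: 300 (200 survivors and 100 caregivers);
- Photovoice group: 50 survivors, who are also exposed to the messages;
- "the non-exposure group (i.e., burn survivors [*n* = 250] not exposed to campaign messages").

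The second objective at the end of the Introduction is to assess the campaign's short- and long-term effects on knowledge, attitudes and practices. Section 4 (Data analysis plan) opens with the aim "To compare changes in self-reported outcomes within groups across two time points" and sets the significance rule: "A two-sided *p* < 0.05 indicates statistical significance".

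**The concern.** The powered quantity is an improvement from baseline to follow-up. The study exists to show that the campaign produces such an improvement, yet 250 of the 600 participants (41.7%) are defined by not receiving it. The 478 is about 80% of the full 600, so it cannot be met from campaign recipients alone. The calculation treats the cohort as one body that improves, while the design divides it into people who receive the intervention and people who do not.

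The stakes lie in how the result is read. A study described as having more than 90% power invites the conclusion that a null result means the campaign failed. If the before-after change in recipients rests on about 280 people, a null result carries considerably less weight than the printed power suggests.

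**Working it through.** **Inputs.** From the sample-size paragraph: 478 evaluable, 600 enrolled, 20% dropout, 63% baseline rate, the figure 70%, 5% significance, 91.5% power. From section 4: two-sided testing. From section 2.1: groups of 300, 250 and 50. Assumption: dropout is 20% in every group.

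**Step 1. Reproduce the plan's figures.** Dropout: 478 / 0.8 = 597.5, so 598, printed as 600. Power: the test is not named, so it has to be inferred. A one-sample test of 63% versus 70%, two-sided 5%, with the variance taken at 70%, gives

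power = Φ( |p1 − p0| / √(p1(1 − p1)/n) − 1.96 )

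At n = 478: √(0.70 × 0.30 / 478) = 0.02096; 0.07 / 0.02096 = 3.340; 3.340 − 1.96 = 1.380; Φ = 91.6%. The printed figure is 91.5%, which this formula reaches at n = 476. The match is close, not exact.

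**Step 2. Count who receives the campaign.**

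- Exposure plus Photovoice: 200 + 100 + 50 = 350 enrolled; 350 × 0.8 = 280 evaluable.
- Exposure group alone: 300 × 0.8 = 240 evaluable.
- Shortfall against the stated requirement: 478 − 280 = 198.

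**Step 3. Power at those numbers, same formula and effect.**

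| Evaluable n | Standard error | 0.07 / SE | Power |
|---|---|---|---|
| 478 | 0.02096 | 3.340 | 91.6% |
| 280 | 0.02739 | 2.556 | 72.4% |
| 240 | 0.02958 | 2.366 | 65.8% |

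Other two-sided versions of the one-sample test give 66.5% to 70.0% at 280: arcsine 70.0%, null variance 68.8%, exact 67.8%, continuity-corrected 66.5%.

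**Step 4. Does the drop depend on the inferred test?** Little. For a test whose signal grows with √n, 91.5% power at 478 means a standardised effect of 1.96 + 1.372 = 3.332. At 280 this becomes 3.332 × √(280/478) = 3.332 × 0.765 = 2.550, so power = Φ(0.590), about 72%. At 240 it becomes 3.332 × 0.709 = 2.361, so power = Φ(0.401), about 66%.

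A paired McNemar test with a 7-point change shows a fall of similar order. With 20% discordant pairs, power goes from 93% at 478 to 75% at 280. With 30% discordant pairs, it goes from 80% to 57%; that case does not start from the printed power.

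**Step 5. Detectable change at 280.** Solving (p1 − 0.63) / √(p1(1 − p1)/280) = 3.332 gives p1 of about 0.719, a change of about 9 points (8.9) at 91.5% power.

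**Step 6. The other reading.** Suppose the 7 points are an average over the whole cohort and the unexposed do not change. The exposed must then improve by 7 / (350/600) = 12.0 points. Pooled power stays as printed. Power in the 280 exposed for 63% versus 75% is Φ(0.12 / 0.02588 − 1.96) = Φ(2.68), above 99%.

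**The case against.** **The target population is not stated.** The paragraph attaches the effect to the cohort study, not to the exposed participants. Read as a cohort average, the 91.5% stands, and Step 6 shows that the exposed participants would then be amply powered. This objection holds. It is why the shortfall has to be stated conditionally, and why the paragraph must say which reading is meant.

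**The effect is unclear.** The text calls 63% the rate of poor knowledge, so 63% versus 70% sits awkwardly with an improvement. A fall in poor knowledge from 63% to 56% gives about 87% at 478 with the same formula, not 91.5%. Literal readings of a 70% improvement (for example 37% to 70%, or 63% to 19%) give power near 100% at 478. They do not reproduce the printed figure, so they cannot be its basis. This limits how firmly a replacement figure can be prescribed. It does not remove the mismatch in numbers, and Step 4 needs only the printed 478 and 91.5%.

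**The planned analysis is different.** Section 4 specifies linear mixed models, and a single-proportion test does not describe their power. That is fair, but the criticism applies equally to the printed 91.5%. The point here concerns the stated power on its own basis.

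**The unexposed group may serve as a comparator.** Under an exposed-versus-unexposed calculation the 250 would count. The paragraph does not make that calculation; it is explicitly before-after.

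**A stronger reading to avoid.** A reader might infer that a before-after test pooled over all 478 has power below 50%, because an average shift of 0.07 × 350/600 = 4.1 points gives 45% to 48%. The document does not support this as a finding. Section 4 compares change within groups, so no such pooled test is specified. The figure also needs exactly zero change in the unexposed, which is nowhere stated and is not assured for a population-level campaign expected to reach about 5 million people.

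**Conclusion.** The point holds in conditional form. The plan's arithmetic from 478 to 600 is sound; the fault is a mismatch between the basis of the calculation and the group structure. If the planned effect is the improvement in people who receive the campaign, which fits the stated objective and the within-group analysis best, the printed power is not delivered. It is about 72% with the exposure and Photovoice groups together, and about 66% in the exposure group alone.

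These figures rest on 20% dropout in every group and on the same effect as the one behind 91.5%. They follow both from √n scaling of the printed figures and from the 63% versus 70% test that nearly reproduces them. It would go too far to say without condition that the study has only about 70% power, because the paragraph leaves open a cohort-average effect, under which 91.5% could stand.

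**What to change.** In the sample-size paragraph, state the population, the effect (baseline and follow-up rates of the same quantity) and the test to which the calculation applies. Then take one of two routes:

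- **Change in campaign recipients.** Base the calculation on about 280 evaluable participants (350 enrolled) and leave out the 250 unexposed survivors. Replace 91.5% with the power at that number, about 72% under the assumptions that reproduce the printed figures, or state the detectable change, about 9 points at 91.5% power. Recompute either figure once the effect wording is settled, rather than copying it from this review.
- **Cohort average over all 600.** Say so, and state the change this implies in exposed participants: about 12 points if the unexposed do not change, on the 7-point reading.

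The cost is a rewritten paragraph and, on the first route, a less favourable stated power. No additional participants, visits or data are needed.

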### Phase I: development and implementation of the campaign

2.3

#### Photovoice

2.3.1

##### Sampling

2.3.1.1

To investigate the preliminary effects of Photovoice on the primary and secondary outcomes of interest, we will categorise participants into three groups, as described previously (see Figure 1). As this is only a pilot study and the objective is mostly to co-adapt the Photovoice programme and evaluate its potential in building capacity for a larger evaluation, no sample size calculation has been deemed appropriate (48, 49). This study will also help us determine whether we can maintain an acceptable attrition rate of Photovoice for a future RCT (50). An effective sample size for this study was determined based on the sample size of previous exploratory studies using Photovoice (31).

Consenting baseline participants will be invited to attend the introductory Photovoice workshop via email and/or a telephone call. The invitation letters will be sent via email and/or postal mail. One-to-one meetings will be organised with those who do not want to be in a group setting.

#### Procedure

2.3.2

##### Introductory workshops

2.3.2.1

We will host introductory workshops at the burn and community centres and governmental institutions across Pakistan, where the interviews and focus groups will be held as part of other WP activities. During these workshops, the project will be explained verbally and through the distribution of information leaflets, while any queries will be addressed by the research staff. We will then seek oral and written informed consent and train the participants to use their phone cameras for photography on the same day. Before being disseminated, the training content and the instructions will be pilot tested on a small group of key stakeholders already involved in another WP of the study. Participants without phone cameras will be given disposable cameras and asked to take photos (post-workshop) depicting their realities of being burn survivors and/or having relatives who are burn survivors. Participants will be assured that there are no ‘right’ or ‘wrong’ ways to take a photo and that no professional photographic training will be provided so that the photos reflect the participants’ own views. Once the participants provide their informed consent, Photovoice facilitators (as part of the research team) will call them on a fortnightly basis to check whether there are any safety-related, personal and/or logistical difficulties with taking pictures and whether the participants need additional support. There will be 10 Photovoice facilitators in total, and each facilitator will manage communication and monitor the Photovoice process and safety of five participants from participating centres.

##### Photo reflection workshops

2.3.2.2

Participants will then be invited to the photo reflection workshops. They will be asked to bring three to five of their photos for individual reflection, which will be guided by the following photo-trigger questions: Describe what you see in this Photo: How does this photo make you feel? Why did you take a photo Of this? What does this photo Tell us about your experience with burns? How can this photo provide Opportunities for us and others to improve our lives. The participants will work individually with the facilitators to produce photo captions. At the end of the workshop, the participants will be asked to fill out a questionnaire package based on the baseline measures again and will be invited to the closed local exhibitions.

##### Closed local exhibitions

2.3.2.3

Private exhibitions of the photos will be conducted at the participating centres. These exhibitions will be closed to the public for the following reasons: (1) to protect the participants’ identity, (2) to help build their confidence in displaying their photos, (3) to provide an opportunity to revise their photo captions and (4) to sign consent forms to have photos of themselves blurred/unblurred in preparation for public dissemination and exhibitions. The participants will be given 2 weeks to decide, if needed, and the research assistants will follow up with them. The participants will be asked to fill out the same questionnaire package based on the baseline measures at the end of the closed exhibitions.

##### Training and supervision of Photovoice facilitators

2.3.2.4

The photovoice facilitators will be trained by the corresponding author in collaboration with the Photovoice Worldwide team, which has expertise in developing customised Photovoice training content for research groups and implementing Photovoice projects in both high- and low-resource settings. The training will be organised into two modules: (1) introduction to Photovoice and facilitation and (2) advanced Photovoice training. The first module will cover background information and will introduce basic facilitation skills in the field. It will also identify the need for advanced training of the facilitators. The second module will be more interactive and will mainly focus on role-plays to familiarise facilitators with the possible ethical (i.e., power sharing) and/or cultural challenges encountered (i.e., use of culturally appropriate language while facilitating Photovoice workshops) and how to solve them in the field. Following these training modules, a working group including health care professionals, key stakeholders (i.e., key informants and burn survivors) and WP1, WP3 and WP5 leads will be formed, and a co-designed Photovoice toolkit will be developed. This toolkit will be used as a guide for the facilitators to train the rest of the facilitators. The toolkit will include background information on Photovoice, facilitation principles, dealing with ethical and cultural challenges, supervision and social media guidelines, supplementary materials (e.g., information sheet and consent forms) and distress and debriefing policies for the facilitators. Follow-up training for the facilitators will also be organised depending on the need. Supervision of the facilitators will be managed by the clinical psychologist of the team on a weekly basis. In-person and online group or one-to-one supervision meetings will be organised to discuss the facilitation process and communication between facilitators and burn survivors during the Photovoice process.

### Phase III: public dissemination of campaign messages through social media channels and community health education sessions

2.4

The priority areas for phase 3 will be determined through the findings from the photo reflection workshops and the interviews social media and health communication campaign content.

In phase 3, the participants (burn survivors) will be given instructions to continue taking photos using their mobile phones after the Photovoice workshops. They will be asked to take pictures of meaningful moments in their daily lives and reflect upon what the photos mean/represent. These instructions will also be pilot tested on a small group of individuals before being disseminated. The participants’ photos from the closed local exhibitions (based on consent) and the new photos that they capture through their mobile phones will be posted on the project website and on social media. There will be a moderation procedure in place. The research assistants will moderate online interactions by monitoring comments and responding to posts. Photos and/or stories with dedicated hashtags will be released at various high-activity times of day. Posters and/or leaflets about the social media accounts will be displayed across public spaces, such as schools and workplaces, to generate more interest in the campaign.

Health messaging will be promoted through organic and paid posts on main social media sites to increase engagement with the audience. A central website will be maintained on WordPress to host the main messages on burn prevention and first aid and will be used as a landing page for the audience to acquire more information. The website will also serve as a central repository for social media content and links for future use. The overall objective is to increase audience engagement with the campaign through likes, comments and shares.

We will run a comprehensive marketing campaign to promote the messages on Facebook, Instagram and Twitter. The promotional content will include video animations, audio/visual stories and infographics. The campaign will promote the content of the campaign and drive traffic to the project website. Broadly, we estimate to reach ~5 million people in Pakistan.

In addition to the online campaign, we will conduct health education sessions for the most vulnerable target audiences at schools, community centres, workplaces, factories and burn centres. These health education sessions will target key informants and stakeholders, aside from burn survivors and their family members. A comprehensive social media messaging campaign will support this in-person communication by providing a centralised location to access more information for burn prevention and first-aid measures. We will also liaise with journalists, TV presenters, radio programmers and bloggers to publicise the campaign. We will ensure that captions to complement photographs, stories and hashtags are culturally sensitive and translated into the study languages.

## End of project exhibitions (nationwide)

3

Finally, we will organise a series of end-of-project exhibitions across the designated research sites in Pakistan to which a broad range of stakeholders, community workers, carers, health care professionals, policymakers and journalists will be invited. With their consent, these end-of-project exhibitions will provide a platform for the participants and others exposed to Photovoice content to talk about their experiences. We will also liaise with journalists, TV presenters, radio programmers and bloggers to disseminate the exhibitions on a national scale. Participants who took part in the Photovoice process will be asked to fill out the same questionnaire package based on the baseline measures at the end of the public exhibitions.

## Data analysis plan

4

To compare changes in self-reported outcomes within groups across two time points (see Table 1) in the sample (*N* = 600), we will implement linear mixed-effects models implemented in R (R version 3.6.1) (51) using the lme4 package and in SAS 9.4. This method considers correlations within participants, allowing them to be modelled appropriately. It also estimates within-subject variability, in addition to estimating model parameters. The method can handle and model missing outcome data under the assumption that the data are missing at random. The mixed model uses a longitudinal data structure that includes both fixed and random effects, and baseline measurement is usually included as a covariate. Time will be included in the model as an interacting categorical variable to observe any time-varying trends. Cohen’s *d* for the effect of Photovoice will be calculated as the difference between baseline-corrected estimated means divided by the pooled standard deviation. A two-sided *p* < 0.05 indicates statistical significance. In addition, demographic variables, such as age, education, gender, marital status, geographic location (i.e., rural vs. urban residence) and household situation (i.e., living with a single and/or an extended family) will be included in the linear mixed models to test for potential moderating and mediating effects on behavioural intention related to burn prevention and first-aid practices. A stepwise selection of the variables will be conducted to determine which variables to keep in the model. As we add the variables, we will immediately eliminate those that do not reduce the Akaike information criterion (AIC) by using the *stepAIC* R function from the library *MASS*. If two or more independent variables in a model are found to be strongly correlated, a variance inflation estimate of less than 5 will be used to determine whether collinearity is present. If the relationship is found to be non-linear, attempts will be made to model the outcome data via the use of splines or polynomials in the *nlme* package in R. The normality of residuals will be assessed graphically using histograms and Q-Q plots. Detailed statistical analyses following Good Clinical Practice: Consolidated Guidelines ICH E9 (52) and Medical Research Council guidelines for developing complex interventions (53) will be described in the statistical analysis plan, which will be finalised before the data lock stage.

In line with the flexibility of the Photovoice approach as a participatory action research method, we decided to follow reflexive thematic analysis based on Braun and Clarke’s six-phase approach (54), with NVivo software supporting data management and coding. All reflection sessions and exhibitions will be audio-recorded, transcribed verbatim and pseudonymised. Two researchers will independently code a subset of transcripts to enhance rigour and then collaboratively develop an analytical framework. Both inductive and deductive coding will identify emergent themes. Thematic analysis will be conducted on captions, participant narratives and social media comments. Special attention will be given to potential group differences (e.g., male vs. female participants, urban vs. rural residence, severity of burn injuries, and communication or health literacy differences). Data analysis will occur in parallel with data collection. Thick descriptions of the context of each workshop and the interactions with each participant will be documented in field notes. The team will agree when data saturation has been reached.

Social media metrics and textual analysis of photo captions and viewer comments will be employed to determine audience reach and engagement. These metrics will also provide insights into perceptions, knowledge and attitudes related to burn survivors and their experiences. The analytics dashboards provided by each social platform will be used to gather key metrics. The main metrics include likes, comments, shares and emojis. Specifically, the comments will be used for thematic analysis to extract more narratives, stories and lived experiences. Overall, a triangulation approach will be used to integrate the results from the different data sources, provide a comprehensive overview of the findings and enhance confidence in the conclusions (55).

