**Methods and analysis:**

This cohort study will follow 600 participants (*n* = 600; *n* = 500 burn survivors; *n* = 100 caregivers) with three measurement points at 6- to 12-month intervals. The primary outcomes are knowledge, attitudes and practices regarding burn injuries. The secondary outcomes are meaning in life; gratitude, resentment and appreciation; hope; optimism; temporal satisfaction with life; coping strategies; social interaction anxiety; self-stigma and resilience, measured using the Meaning in Life Questionnaire, the Gratitude, Resentment and Appreciation Scale, the Adult Workers Hope Scale, the Patient Optimism Scale, the Temporal Satisfaction with Life Scale, the COPE Inventory, the Social Interaction Anxiety Scale, the Self-Stigma Scale and the Brief Resiliency Scale, respectively. The participants are grouped as follows: the exposure group (i.e., burn survivors [*n* = 200] and caregivers [*n* = 100] exposed to campaign messages), the non-exposure group (i.e., burn survivors [*n* = 250] not exposed to campaign messages) and the Photovoice group (i.e., burn survivors [*n* = 50] who participate in Photovoice and are exposed to the campaign messages). This design evaluates the impact of the health communication campaign and determines whether Photovoice has any additional effects on the primary and secondary outcomes.

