##### Burn survivors

2.2.4.1

The following are the inclusion criteria for burn survivors:

Adults aged 18 years and aboveRecent (i.e., within the past 3 months) and/or past experience of a burn injuryResides in one of the seven research sitesAble to provide consent and participate in the mixed methods study, which requires their engagement in project activities, including surveys, Photovoice reflection workshops and closed/open exhibitions depending on the group to which they are assignedFor those involved in the Photovoice group, an additional criterion includes willingness to engage with participatory creative methods, such as photography and storytelling, as well as availability to attend a minimum number of Photovoice workshops.

The following are the exclusion criteria:

Burn survivors with intentional and/or self-inflicted injuries will be signposted to the available services for further help and will not be included in the study.

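### The stated analysis and the sample size are pre-post within groups, so the between-group campaign contrast that the design claims is neither named nor powered

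*Protocol article*

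**What the plan says.** The abstract describes an exposure group (200 survivors and 100 caregivers), a non-exposure group (250 survivors) and a Photovoice group (50 survivors), and concludes: "This design evaluates the impact of the health communication campaign and determines whether Photovoice has any additional effects on the primary and secondary outcomes". Section 2.1 (Research design) repeats this, with the outcome indicators measured "as well as psychological variables and health information-seeking variables, among the following groups: the exposure group" and the other two groups.

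Section 4 (Data analysis plan) states the purpose of the linear mixed models as "To compare changes in self-reported outcomes within groups across two time points (see Table 1"), in the sample of 600. On the model it adds that "baseline measurement is usually included as a covariate" and that "Time will be included in the model as an interacting categorical variable to observe any time-varying trends". It does not say what time interacts with. Cohen's d "for the effect of Photovoice will be calculated as the difference between baseline-corrected estimated means divided by the pooled standard deviation", with no comparator named.

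The sample size paragraph, at the end of section 2.2.5.10, is "based on a comparison of the baseline and follow-up measures of the primary outcome, knowledge of burn-related prevention, in this cohort study". It gives 478 evaluable participants, 63% poor knowledge at baseline, a 70% improvement, 5% significance and 91.5% power at 24 months, raised to 600 for 20% dropout.

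**The concern.** Campaign impact is a statement about exposed people relative to what would have happened without exposure. The 250 non-exposed survivors are there to supply that reference, but the stated comparison and the sizing both leave them out. Change from baseline within the exposed group contains the campaign effect plus anything else that moves scores over 24 months: familiarity with a repeated questionnaire, secular change and, for the psychological scales, adjustment after injury, since burns within the past 3 months are eligible.

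If the plan is followed as written, a significant change in the exposed group could be reported as campaign impact when there is none. A team that later turned to the between-group contrast would find that the sample size had not been calculated for it.

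**Working it through.** **1. What the sample size compares.** Inputs from the sample size paragraph: 63%, 70%, 5% significance (two-sided per section 4), 91.5% power. Read 63% and 70% as the two proportions in a one-sample test, with the variance at 70%:

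- n = 0.70 × 0.30 × ((1.960 + 1.372) / 0.07)² = 476, against 478 stated.
- Power at n = 478: 0.07 × √(478/0.21) − 1.960 = 3.340 − 1.960 = 1.380, giving 91.6% against 91.5% stated.
- Dropout: 478 / 0.80 = 598, about 600.

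Reading 63% and 70% this way is an inference from the match. A paired (McNemar) test of 63% v 70% also gives about 478 if the within-person correlation is about 0.53, which is not stated. Neither reading has a comparison group. A two-arm comparison of 63% v 70% at 91.5% power needs about 1,008 per arm.

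**2. What a within-group test does when the campaign has no effect.** Assumptions, none from the protocol except the 20% loss: a background shift of 0.2 SD common to all groups and a test-retest correlation of 0.5, so the SD of change is √(2 × (1 − 0.5)) = 1. Exposed completers: 300 × 0.8 = 240.

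- 0.2 × √240 − 1.960 = 3.098 − 1.960 = 1.138, so about 87% of trials are significant.
- Range by size of shift: 0.1 SD gives 1.549 − 1.960 = −0.411, about 34%; 0.3 SD gives 4.648 − 1.960 = 2.688, over 99%.
- Exposed survivors alone (160): 0.2 × √160 − 1.960 = 0.570, about 72%.
- Between-group tests under the same 0.2 SD shift (20,000 simulated trials): 5.1% for exposed v non-exposed survivors and 5.4% for Photovoice v exposed survivors. A shift common to all groups cancels.

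**3. What the between-group contrasts can detect.** After 20% loss: exposed survivors 160, non-exposed 200, Photovoice 40.

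| Contrast | d at 80% power | Power for 63% v 70% |
|---|---|---|
| Exposed v non-exposed survivors (160 v 200) | 2.80 × √(1/160 + 1/200) = 0.30 | 28% |
| Photovoice v exposed survivors (40 v 160) | 2.80 × √(1/40 + 1/160) = 0.50 | 12% |

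For the 28%: the pooled proportion is (160 × 0.70 + 200 × 0.63)/360 = 0.661; the SE under no difference is 0.0502 and under the alternative 0.0498; (0.07 − 1.960 × 0.0502)/0.0498 = −0.57, giving 28%.

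**The case against.** The strongest reply is that the document does not rule out a between-group analysis. Cohen's d for Photovoice is a difference between baseline-corrected means, which is most naturally a difference between groups. Time enters as an interacting variable, and group could be its partner. Baseline as covariate with two follow-ups as outcomes is a common between-group model and may explain the reference to two time points in a study with three measurements. Detailed analyses are deferred to a statistical analysis plan that is not shown. Sections 1 and 2.3.1.1 describe the Photovoice effects as preliminary and that part as a pilot without a sample size calculation.

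Much of this stands. A reader might infer that the plan runs one pooled test on all 600, or that the analysis cannot show any campaign or Photovoice effect. The text supports neither: it says within groups, describes no pooled test, and the data and model could deliver the contrast if it were specified. For the same reason, a loss of power from pooling exposed and non-exposed people cannot be charged to the plan. The low power for Photovoice is also largely acknowledged.

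The deferral does not remove the remainder. The direction of comparison is not left open: the protocol states it as within groups and sizes the study accordingly. An analysis plan that switched to between-group contrasts would depart from that statement and inherit a sample size calculated for something else.

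It is also fair to say that the 0.2 SD shift is assumed, and that recovery from injury is a weak explanation for change in knowledge, the outcome used for sizing. Repeat testing and secular trend are the more plausible sources for that outcome.

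**Conclusion.** The concern holds as a mismatch between claim and stated comparison. The claim is between groups; the stated comparison and the sizing are pre-post. The campaign contrast is not named, the 91.5% power does not apply to it, and the Photovoice effect size has no named comparator.

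The 87% rests on an assumed common shift and change SD, and runs from about 34% to over 99% as the shift goes from 0.1 to 0.3 SD. That within-group change cannot be attributed to the campaign does not depend on those values. The 28% rests on reading the sample size as 63% v 70%, which the arithmetic supports but the text does not spell out.

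Naming the contrast does not make it causal. Allocation is not described as random, so background change may differ between groups and need not cancel as in the illustration. The Photovoice group is further selected, since for it "an additional criterion includes willingness to engage with participatory creative methods, such as photography and storytelling".

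**What to change.** - In section 4, replace the within-group aim with a primary contrast of exposed v non-exposed survivors, from a mixed model with group, time, group × time and baseline score. Adjust for the demographic variables already collected, because allocation is not described as random.
- Analyse the 100 caregivers separately as pre-post description; the non-exposure group contains none.
- Name exposed survivors as the comparator for the Photovoice Cohen's d, report it as a preliminary estimate with a 95% confidence interval, and change 'determines' to 'estimates' in the abstract.
- Report within-group changes as descriptive.
- State that the 91.5% power applies only to the pre-post comparison, and give the precision of the contrasts after 20% loss: 80% power for d of about 0.30 (160 v 200) and about 0.50 (40 v 160), with about 28% power for 63% v 70% in the first.

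The cost is wording in the protocol and the analysis plan before data lock; no new data or participants are needed. The downside is that the primary contrast is less precise than the pre-post figure suggests and remains observational, so the campaign claim has to be worded accordingly.
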